## Abstract

**Introduction:**

While breast cancer outcomes are improving steadily in younger women due to advances in screening and improved therapies, there has been little change in outcomes among the older age group. It is inevitable that comorbidities/frailty rates are higher, which may increase the risks of some breast cancer treatments such as surgery and chemotherapy, many older women are healthy and may benefit from their use. Adjusting treatment regimens appropriately for age/comorbidity/frailty is variable and largely non-evidence based, specifically with regard to rates of surgery for operable oestrogen receptor-positive disease and rates of chemotherapy for high-risk disease.

**Methods and analysis:**

This multicentre, parallel group, pragmatic cluster randomised controlled trial (RCT) (2015-18) reported here is nested within a larger ongoing ‘Age Gap Cohort Study’ (2012-18RP-PG-1209-10071), aims to evaluate the effectiveness of a complex intervention of decision support interventions to assist in the treatment decision making for early breast cancer in older women. The interventions include two patient decision aids (primary endocrine therapy vs surgery/antioestrogen therapy and chemotherapy vs no chemotherapy) and a clinical treatment outcomes algorithm for clinicians.

**Ethics and dissemination:**

National and local ethics committee approval was obtained for all UK participating sites. Results from the trial will be submitted for publication in international peer-reviewed scientific journals.

**IRAS reference:**

115550.

**Trial registration number:**

European Union Drug Regulating Authorities Clinical Trials (EudraCT) number 2015-004220-61;Pre-results. Sponsor's Protocol Code Number Sheffield Teaching Hospitals STH17086. ISRCTN 32447*.

Strengths and limitations of this studyThe two evidence-based decision support interventions (DESIs) for women over 70 years diagnosed with breast cancer who are offered a choice of primary endocrine therapy or surgery (plus adjuvant endocrine therapy, hereafter termed surgery/AET, antioestrogen therapy) or chemotherapy versus no chemotherapy are, to the best of our knowledge, the first of its kind worldwide.The web-based clinical outcomes management algorithm is the first of its kind and allows patient age, comorbidities, frailty and cancer characteristics to be considered in predicting breast cancer survival and cancer outcomes.A limitation of the trial will potentially be selection bias from recruitment and poor uptake/utilisation of the DESIs at intervention sites.A second limitation may be an inability to demonstrate a benefit in terms of cancer survival rates without at least 5–10 years follow-up or an overall survival advantage due to the competing causes of death in this age group.

## Introduction

### Background and rationale

Breast cancer is the most common cancer in women in the UK, with over 53 000 new cases being diagnosed in the UK each year.^1^ Of these, 16 000 women will be over the age of 70, a figure which is rising steadily as the UK population ages.^2^ While breast cancer outcomes are improving steadily in younger women due to advances in screening and improved therapies, there has been little change in outcomes in this older age group of women. The UK lags significantly behind other European countries in its outcomes for these women. There is a wide variation in practice in the management of breast cancer in older women.^3^ The gold standard of care for early breast cancer is surgical removal of the primary cancer (mastectomy or conservation surgery), and diagnostic or therapeutic axillary nodal surgery followed by stage and immunophenotype appropriate adjuvant therapies (chemotherapy, trastuzumab, antioestrogens and radiotherapy) to reduce the risks of disease recurrence. There is consistent evidence that older women are less likely to receive surgery, chemotherapy, radiotherapy and trastuzumab, based on the premise that there is less evidence of efficacy and a greater risk of treatment morbidity.^4^ In the case of surgery, up to 40% of older women do not undergo surgery for their breast cancer, and their treatment is mainly with antioestrogen tablets alone, known as primary endocrine therapy (PET).^5^ While it is inevitable that in older women, comorbidities and frailty rates are higher, and which will increase the risks of some breast cancer treatments, such as surgery and chemotherapy, many older women are healthy and will benefit in terms of breast cancer outcomes from their use. Selection of appropriate age, comorbidity and frailty-adjusted treatment regimens is highly variable, largely non-evidence based and often fails to adequately consider the needs or wishes of patients. Two key areas of local practice variation are rates of surgery for operable oestrogen receptor (ER) positive disease and rates of chemotherapy for high-risk disease. PET rates vary fourfold between UK centres^3^ and are not accounted for by case mix adjustment. Similarly, rates of chemotherapy vary 10-fold.^4^

Recent reports have advocated the use of PET only in the very old or frail.^6^ Current national guidelines state that patients with operable breast cancer should be treated with surgery, and not PET, ‘irrespective of age’ unless this is precluded by comorbidities^7^; while the International Society of Geriatric Oncology and European Society of Breast Cancer Specialists recommend that PET should only be offered to patients with a ‘short estimated life expectancy (less than 2 to 3 years), who are considered unfit for surgery… or who refuse surgery.’^8^ However, as a large number of older women are treated with PET in UK and other countries, it is not clear whether this guidance is being followed consistently. PET is associated with high rates of patient satisfaction and low treatment morbidity but in the medium and long term some women may need a change of therapy once antioestrogen resistance develops.^9^ Randomised trials and a recent Cochrane review have shown that surgery (plus adjuvant antioestrogens hereinafter termed surgery/AET, antioestrogen therapy) and PET have equivalent overall survival rates.^10 11^ However, for fitter women with a longer predicted life expectancy, there is evidence that breast cancer specific survival rates are inferior with PET.^12^ For very frail women where surgery would be unsafe or poorly tolerated, PET is the clear choice in women with oestrogen-sensitive disease.^12^

For women at intermediate or higher risk of surgery complications, there is a complex series of trade-offs to be made for each patient. The decision must balance the risks of surgical morbidity (pain, risks associated with hospitalisation, surgical complications) but with a greater certainty of local disease control, against the minimal morbidity with PET but a risk of later local disease progression and the need for a change of treatment to either surgery or alternate AET.^13–15^

Chemotherapy utilisation is also very low in women over 70 (14%)^4^ and almost non-existent in women over 80, even in those where high phenotypic risk is present (high grade, node positive, ER negative, HER2 positive).^4^ Rates of chemotherapy can vary widely between UK breast units, between 6% and 60% in high-risk women.^16^ This reflects the fact that most of the randomised trials have upper age cut-offs at age 70 or recruit very poorly in this age group, meaning there is little evidence of whether it is effective or not. In addition, there is evidence of an increased risk of significant complications such as neutropenic sepsis in older women.^17^ This clearly suggests that guidelines for best practice are required. The primary tool used by oncologists to determine the likely benefit of chemotherapy on a patient level basis is Adjuvant!Online,^18^although this has been shown to be inaccurate in older women.^19^ The more recently developed PREDICT tool^20^ performs better in this age group but has limited functionality for taking comorbidity and frailty into account.

This cluster randomised trial will evaluate the implementation of two (‘complex’) decision support interventions (DESIs) designed to be used by both clinicians and patients to assist in the decision making about treatment for early breast cancer in older women.

### The Bridging the Age Gap study

The Bridging the Age Gap study^21^ is an NIHR (National Institute for Health Research) funded programme of research (2012-18RP-PG-1209-10071) examining breast cancer management in older women with the ultimate aim of improving outcomes by providing high-quality evidence to support treatment decision making in this age group.

The study protocol reported here focuses exclusively on the cluster randomised trial part of the wider Bridging the Age Gap study.^21^ The study group has developed two patient-facing DESIs based on a systematic evidence summary, expert reference group consultation, patient interviews^22–24^ and questionnaires about informational needs and preferences and extensive user and field testing with both healthy older women and older women who had faced the decision relating to the choice of surgery/AET or PET in frailer women with ER-positive breast cancer, and the decision regarding use of adjuvant chemotherapy in fitter women with high-risk cancers. Each DESI includes a clinician-facing clinical management algorithm and two patient-facing decision aids (PtDAs). The clinician-facing management algorithms derive from detailed cancer registry outcome data linked to treatment-related morbidity and patient and cancer characteristics from the UK cancer registry (2002–2010) for two UK regions (Northern and Yorkshire and East Midlands) which are representatives of the UK population as a whole in terms of demography, population structure and deprivation. This is a large diverse area, representing 23% of the UK population.^25^ These online algorithms allow patient age, comorbidities, frailty and cancer characteristics to be considered by a clinician in predicting survival and cancer outcomes and to help inform breast cancer management decisions for older women.^25^ The PtDAs are in the form of a booklet and a (brief) option grid for the clinical decision in question.^26 27^

The trial will evaluate these tools in a cluster randomised trial across 53 UK breast units according to the study schematic (figure 1).

**Figure 1 F1:**
[figure not shown]
Overview of the cluster randomised controlled trial. PET, primary endocrine therapy.

The aim of this trial is to evaluate if, how and to what extent, the use of the DESIs embedded as ‘standard of care’ within intervention arm sites improves quality of life (QoL), decision quality (integrating knowledge, attitudes and decision made), coping and illness representations, and reduces decision regret, thus indicating improved informed decision making of older women about treatment options for their breast cancer.

To our knowledge, this is the first randomised controlled trial (RCT) to have been undertaken to explore this issue.

### Objectives

The objectives are:To assess the effectiveness of the implementation of DESIs^26 27^ in clinical practice in terms of improving patient QoL, decision quality (integrating knowledge, attitudes and decision made), coping and illness representations, and reducing decision regret, thus indicating improved informed decision making.To determine if how, or to what extent, the clinical outcomes management algorithm impacts on clinical decision making among clinicians (change in PET/surgery rates and chemotherapy rates).To determine whether the DESIs are effective in improving short, medium and long-term cancer outcomes in this age group of women (treatment morbidity and overall and disease-specific survival).To assess the utility and uptake of the DESIs from the perspective of both clinicians and patients by undertaking a formal process evaluation.

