### The RCT study

The intervention comprises implementation of a package of two DESIs for the PET versus surgery/AET, or chemotherapy versus no chemotherapy decisions. Each DESI includes an online algorithm for treatment outcomes, and two PtDAs—a booklet and a brief option grid.^26 27^ Each DESI is a complex intervention, including training for the clinician (breast surgeon, medical oncologist, breast care nurses) on the use of the algorithm (surgeons and medical oncologists only) or PtDAs, and the clinician and patient decide which, if any, of these elements they wish to use to assist the decision-making process, the intention being for the intervention to be used as part of everyday clinical practice/pathway within the intervention sites.

Each online algorithm includes functionality to adjust outcome prediction according to patient age, comorbidity, frailty, tumour stage and ER status and which gives outputs of 2 and 5-year overall and breast cancer specific survival. The algorithms were developed in the earlier phase of the Age Gap study^25^ and were designed to guide clinicians and their patients in the treatment of:frailer older women with ER-positive breast cancer to optimise treatment with either PET or surgery/AET;fitter older women who have already had primary surgery and been found to have high-risk cancer characteristics (eg, ER-negative, HER2-positive or node-positive breast cancer) to optimise treatment with either adjuvant chemotherapy or no adjuvant chemotherapy (note the term chemotherapy includes chemotherapy +/− trastuzumab if appropriate).

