### Randomisation

Randomisation is at breast unit level, stratified by high and low PET and chemotherapy rates. It was therefore not possible to blind the investigators or the study sites to the allocation of participants. Data for this stratification have been derived from the wider cohort study which has collected data on treatment rates for both PET versus surgery/AET and chemotherapy versus no chemotherapy.

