### Control arm

Usual standard practice for older women (>70 years) diagnosed with breast cancer with no change to normal treatment decision-making practice.

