### Intervention arm

Usual standard practice for older women (>70 years) diagnosed with breast cancer plus optional clinician and patient access to the package of DESIs which will have been made available to these units to adopt as their standard of care.

In the run into the trial period (June–December 2015), clinical teams (clinicians, research and breast nurses) from the participating sites attended a training event to enhance concordance with the study protocol (control group) and provide additional training on shared decision making and the use of the DESIs (intervention group). This comprised a 2-hour practical workshop which consisted of presentations, demonstrations and discussion based on the MAGIC programme.^46^

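### Objective 2 asks how far the clinician algorithm changes treatment rates, but the randomised comparison can only give the effect of the whole decision support package

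*Protocol article*

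**What the plan says.** The article lists four objectives (Introduction, Objectives). The first, third and fourth concern the DESIs. Only the second names a single component: it asks whether, how and how far "the clinical outcomes management algorithm impacts on clinical decision making among clinicians (change in PET/surgery rates and chemotherapy rates".

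The trial section describes what is delivered: "The intervention comprises implementation of a package of two DESIs for the PET versus surgery/AET, or chemotherapy versus no chemotherapy decisions". It then gives the content: "Each DESI includes an online algorithm for treatment outcomes, and two PtDAs—a booklet and a brief option grid". Clinician training is part of each DESI, and use is left open, since "the clinician and patient decide which, if any, of these elements they wish to use to assist the decision-making process".

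On allocation, "Randomisation is at breast unit level, stratified by high and low PET and chemotherapy rates" (Randomisation). The control arm is "Usual standard practice for older women (>70 years) diagnosed with breast cancer with no change to normal treatment decision-making practice" (Control arm). Intervention units add "optional clinician and patient access to the package of DESIs" (Intervention arm). Teams from both arms attended a training event. For control units its purpose was adherence to the protocol; for intervention units it was also to "provide additional training on shared decision making and the use of the DESIs (intervention group".

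The Data analysis section compares the DESI and control groups by intention to treat. The text on data collection (under Primary outcome measure) says that the follow-up data will show whether the DESIs shift treatment choices at intervention sites relative to control sites.

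**The concern.** Objective 2 puts a question of degree, with a named rate outcome, about one element of a bundle. The other elements act on the same outcome. The booklet and option grid deal with the same two choices, PET or surgery and chemotherapy or none, that objective 2 would count. The algorithm's output can also be printed for use in counselling the patient, so the clinician and patient routes overlap.

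If the objective is answered as worded, a shift in rates could be credited to the algorithm when the patient aids or the training produced it. Equally, a null result could be held against the algorithm when the package as a whole was little used. Either reading would matter to anyone deciding whether to adopt the online tool without the rest.

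**Working it through.** The article gives no figure for this objective, so there is none to reproduce. The sample size section concerns the quality of life score and has no bearing here. The check sets the objective beside the randomised contrast.

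**1. Elements that differ between the arms** (The RCT study; Control arm; Intervention arm)

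| Element | Control units | Intervention units |
|---|---|---|
| Online algorithm (A) | not offered | offered, optional |
| Booklet (B) | not offered | offered, optional |
| Option grid (G) | not offered | offered, optional |
| Training in shared decision making and DESI use (T) | not given | given |

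All four entries change together. No unit is described as receiving A alone, or B, G and T without A.

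**2. What the contrast identifies.** Let R(·) be the expected PET, surgery or chemotherapy rate under a given offer. The trial observes R(A+B+G+T) and R(none), so it estimates

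package effect = R(A+B+G+T) − R(none).

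The algorithm's effect needs either R(A) − R(none) or R(A+B+G+T) − R(B+G+T). Neither R(A) nor R(B+G+T) is observed under randomisation.

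**3. The simplest case.** Suppose the four elements acted additively, with no interaction. Then package effect = a + b + g + t, which is one equation in four unknowns. Recruiting more units or more women makes the sum more precise and leaves a undetermined. If the elements interact, there are more unknowns.

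**4. Whether other parts of the plan supply the missing information.**
- *Use within intervention units.* Clinician and patient choose which elements to use after allocation, so any contrast based on use is non-randomised. It could not stand in for a randomised estimate of a.
- *Process evaluation.* This covers 16 sites and looks at implementation, usefulness, acceptability, and barriers and facilitators. It can inform how the algorithm is used. It gives no causal estimate of a change in rates.
- *Statistical analysis plan.* It is not shown. It could add modelling assumptions, but it could not turn one bundled contrast into a randomised estimate for one component.

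**5. Consistency within the article.** Three of the four objectives, the statement on treatment patterns in the data collection text, and the Data analysis section all refer to the DESIs or to the DESI group against control. Objective 2 is the one statement out of line.

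**The case against.** The best defence is that a pragmatic trial of a complex intervention need not separate its components, and that the article plans no algorithm-only estimate. Where it says how treatment patterns will be examined, it states the package contrast. That stands. It confines the point to the wording of one secondary objective and means that no design change is called for. It does not rescue the objective, which asks how far one named component changes rates.

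A second defence is that the question of *how* is served by the process evaluation. That also stands, but it leaves the question of degree unanswered.

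A reader might infer four stronger criticisms. The document does not support them:
- *The trial will report a causal effect of the algorithm.* Nothing shown plans this; the stated comparison is DESI against control.
- *The Data analysis section contradicts the word change in objective 2.* That section gives no model for treatment rates; the continuous outcomes it names are scores. Change can also mean a difference between arms, and the detail may lie in documents not shown.
- *The plan relies on comparing algorithm users with non-users.* No such comparison is proposed. It appears above only to show that it could not fill the gap.
- *Rates should be estimated over every eligible woman at each unit.* Women enter by receiving a study pack and consenting, and the article itself names selection bias from recruitment as a possible limitation. Nothing shows that treatment is recorded in the trial for eligible women who did not enrol.

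**Conclusion.** The point holds as a mismatch between objective 2 and the randomised contrast. The trial can estimate the effect of offering the package with training on PET/surgery and chemotherapy rates. It cannot estimate the algorithm's separate contribution.

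The size cannot be put as a bias in percentage points, because the algorithm-only effect is not identified at any sample size. The consequence is for what may be concluded on this objective. The primary quality of life comparison, its sample size and the randomisation are untouched.

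The conclusion rests on the article's description of two arms and one bundled intervention. It would change only if the full protocol contained an arm, factor or phase isolating the algorithm, and the article gives no sign of one.

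**What to change.** Reword objective 2 along these lines: to estimate the effect of offering the DESI package, with its training, on PET/surgery rates and chemotherapy rates among enrolled women, compared between intervention and control units by intention to treat.

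Adjust that comparison for each unit's pre-trial PET and chemotherapy rates. The Randomisation section says the wider cohort collected these data and that they were used to stratify. This is an improvement in the analysis and not the correction of an error, and it needs no new data.

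Report use of the algorithm descriptively alongside the process evaluation. Label any algorithm-specific analysis exploratory and non-randomised, and draw no causal conclusion about a single element from it.

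The cost is a change of wording in the objective and the matching lines of the analysis plan. The price is a narrower claim: the trial will speak to the package and will not say what the algorithm does by itself.

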### Hypotheses

Use of the DESIs will improve the QoL in older women with operable breast cancer and ultimately improve cancer outcomes.Older women faced with a choice of treatment decisions for their breast cancer will report an improved decision quality and shared decision-making experience and less decision regret using DESIs compared with older women who receive usual clinical decision-making support.Use of evidence-based DESIs will improve short and longer term outcomes by improving treatment personalisation to a woman's health, fitness and cancer characteristics and by improving the quality of decision making, and reduce the heterogeneity of practice across the UK.Women in the intervention sites will express more positive illness representations (eg, increased personal control, positive emotional consequences, less overall threat) and increased use of engagement coping strategies compared with women from the control sites.

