An independent data monitoring committee (DMC) comprising three experienced academic clinicians oversees the study and monitors trial conduct and safety and potential harm and has access to all study data; the role being to provide recommendations for trial changes (or closure). Data collection is being undertaken by trained clinical staff within each of the participating sites. The study data manager and study monitor also undertake regular site visits to outline the study protocol, ensure protocol adherence and monitor data collection and completeness. Data collection for the study includes detailed information about the patients and their cancer at the time of diagnosis: age, comorbidity (Charlson comorbidity index,^32^ frailty—The Barthel Index (ADL, activities of daily living)^33^ and instrumental activities of daily living scores (IADL)^34^), cognitive status (Mini-Mental State Examination),^35^ baseline QoL (EORTC QLQ C30,^31^ EORTC breast cancer-specific QoL questionnaire (QLQ-BR23),^36^ EORTC QoL questionnaire module for older people with cancer (QLQ-ELD14),^37^ EuroQol Group EQ-5D^38^), tumour stage, grade and receptor status. Treatment details are recorded including the type of surgery to the breast and axilla, use of adjuvant therapies (chemotherapy, radiotherapy, trastuzumab and hormonal therapies), including doses and adverse effects recorded using the Common Terminology Criteria for Adverse Events grading system. Follow-up is at baseline, 6 weeks, and 6, 12, 18 and 24 months after diagnosis/consent. Cancer outcomes, QoL and adverse events are recorded at each visit and in the longer term, women are asked to sign a consent form to permit the trial to collect their Cancer Registry data which will be collected 5 and 10 years following diagnosis and consent to the study. These data will permit us to look at whether using the DESIs alters patterns of treatment decision making between control and intervention sites and whether these impact on long-term outcomes. As such this is a uniquely detailed evaluation of such DESIs.

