A series of exploratory subgroup analyses using a marginal GLM with coefficients estimated using GEE with robust SEs and an exchangeable autocorrelation matrix, with the primary outcome the mean global health status/QoL score (questions 29+30 of EORTC QLQ-C30^31^) at 6-month postdiagnosis/consent randomisation as the response will be carried out. An interaction statistical test between the randomised intervention group and subgroup to directly examine the strength of evidence for the treatment difference between the treatment groups (intervention vs control) varying between subgroups will be undertaken. Age subgroup (75–79, 80–84, 85–89 and 90+ years) and comorbidity levels (based on the modified Charlson comorbidity score^32^) will be the only a priori defined subgroups to be considered for interaction test. Subgroup analysis will be performed regardless of the statistical significance on the overall intervention effect (intervention vs control).

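### Hypothesis 3 claims better personalisation of treatment, but the stated measure is change in PET/surgery and chemotherapy rates, which cannot show whether personalisation improved

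*Protocol article*

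**What the plan says.** Four parts of the protocol article bear on this point.

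- **Hypotheses**, third item: short and longer term outcomes are to improve "by improving treatment personalisation to a woman's health, fitness and cancer characteristics". This is a statement about individual women.
- **Objectives**, second item: the algorithm's effect on clinicians' decisions is given as "change in PET/surgery rates and chemotherapy rates". The section on data collection and outcomes adds that the data will show "whether using the DESIs alters patterns of treatment decision making between control and intervention sites", and names no contrast by fitness.
- **Data analysis**: the exploratory interaction models are fitted "with the primary outcome the mean global health status/QoL score" at 6 months. Age group and modified Charlson score "will be the only a priori defined subgroups to be considered for interaction test".
- **Background and rationale**: "for fitter women with a longer predicted life expectancy, there is evidence that breast cancer specific survival rates are inferior with PET", whereas for very frail women with oestrogen-sensitive disease the same section regards PET as the clear option.

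Charlson index, Barthel ADL, IADL, tumour stage and treatment received are all recorded in both arms (Data collection and outcomes; Table 1).

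**The concern.** Better personalisation means that treatment depends more closely on fitness and disease in the intervention arm than in the control arm. In statistical terms this is an arm-by-fitness interaction with treatment received as the response. A comparison of rates between arms is a main effect. Given the article's own rationale, a DESI that worked as intended could raise surgery in some women and lower it in others, and the main effect would then understate what happened. The converse also holds: a rate could move in one direction for all women alike, with no gain in matching.

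At stake is the reading of the personalisation clause. If rates do not move, the stated measure cannot distinguish a DESI that left decisions alone from one that redistributed treatment between fitter and frailer women. The QoL interaction tests do not fill the gap, because they ask whether the effect on QoL varies by age or comorbidity, not whether treatment followed fitness more closely.

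**Working it through.** **The plan's own figure.** For a 7-point difference, SD 21, two-sided 5% and 90% power, n = 2 × (1.96 + 1.2816)² × (21/7)² = 189.1, so 190 per group. Design effect 1 + (10 − 1) × 0.03 = 1.27, stated as 1.3. Then 2 × 190 × 1.3 = 494, rounded to 50 × 10 = 500. With 20% loss, 10/0.8 = 12.5, so 13 per unit and 50 × 13 = 650. The sample size reproduces and is not in question here.

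**Inputs for the illustration.**
- From the sample size section: 325 women per arm, 13 per unit, ICC 0.03, so design effect 1 + 12 × 0.03 = 1.36. The ICC is the article's value for QoL; using it for treatment received is an assumption.
- From the background: up to 40% of older women do not have surgery.
- Assumed, because the article gives none of them: the fit/frail split, the rates within each stratum and the size of the shifts.

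**Formulas.** Let s be the share of fitter women, and let PET fall by d in fitter women and rise by d in frailer women.
- Change in the overall PET rate = (1 − s)d − sd = (1 − 2s)d. This is zero at s = 0.5.
- Interaction = 2d, with SE = √(sum of p(1 − p)/n over the four arm-by-fitness cells).
- Power ≈ Φ(|effect|/SE − 1.96).

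**Set A: full design effect of 1.36 on both tests.** Control PET is 40% in both strata, or 25% in fitter and 55% in frailer women. Worked case with 40% in both, s = 0.5 and d = 10 points: n per cell = 162.5/1.36 = 119.5; sum of p(1 − p) = 0.24 + 0.21 + 0.24 + 0.25 = 0.94; SE = √(0.94/119.5) = 0.0887; z = 0.20/0.0887 = 2.25; power 62%. The overall rate is 40% in both arms, so that test rejects at 5%.

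| Fit/frail split | d (points) | Rate test | Interaction |
|---|---|---|---|
| 50/50 | 10 | 5% | 62-69% |
| 50/50 | 15 | 5% | 93-97% |
| 50/50 | 20 | 5% | over 99% |
| 60/40 | 10 | 7% | 60-66% |
| 60/40 | 20 | about 15% | over 99% |
| 70/30 | 10 | about 15% | 54-58% |
| 70/30 | 20 | 45-48% | about 99% |

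The ranges span the two sets of control rates.

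**Set B: interaction treated as a within-unit contrast, without inflation.** Control surgery rates are 80% in fitter and 50% in frailer women, split 50/50, with 162.5 per cell. For +10/−10 points: sum of p(1 − p) = 0.16 + 0.09 + 0.25 + 0.24 = 0.74; SE = √(0.74/162.5) = 0.0675; z = 0.20/0.0675 = 2.96; power 84%. With the full 1.36 inflation, SE = 0.0787, z = 2.54 and power is 72%. For an uneven shift of +15/−7.5 points, overall surgery moves from 65% to 68.75%. The rate test (design effect 1.36) then has 14% power and the interaction 93%.

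Across both sets, balanced 10-point shifts give the interaction roughly 60-85% power and the rate test 5%.

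**The case against.** The strongest reply is that the article does not fix an analysis of average rates. The objective does not call the rates overall or unadjusted, the reference to patterns of decision making is loose enough to admit analysis by type of patient, and a condensed article may leave the model for treatment received to the full plan. Also, hypothesis 3 has outcomes as its endpoint and personalisation as the route, and a protocol need not test every step in a mechanism. These points limit the finding to a mismatch between a stated hypothesis and the only treatment measure stated for it. They do not remove it, because nothing in the article relates treatment received to fitness by arm.

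Two stronger readings are tempting and are not supported.

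- A reader might infer that the closed list of subgroups bars any fitness analysis of treatment received. That sentence belongs to a paragraph whose response is 6-month QoL, so it limits the QoL subgroups only. Keeping those few is a defensible choice.
- A reader might infer that opposite shifts would leave the DESIs judged ineffective. The primary outcome is QoL. Knowledge, regret, shared decision making, anxiety, coping, morbidity and survival are also assessed, and a 16-site process evaluation runs alongside. A flat rate would not decide the trial.

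It is also fair to say that the PET/surgery algorithm is aimed at frailer women, so the mix of fitness among women facing that decision is unknown and an even split is only a convenience.

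**Conclusion.** The point holds as a mismatch between claim and measure: rates of PET/surgery and chemotherapy, whether they change or not, cannot show that treatment was better fitted to the woman. Opposite shifts dilute the rate comparison in general and cancel it only when they balance. In the illustration the rate test has 5% power under balance and about 7-48% with 60/40 to 70/30 splits and shifts of 10-20 points. All of these figures rest on assumed splits, rates and shifts, and on an ICC borrowed from QoL. The article reports fourfold variation in PET rates between centres, so the ICC for treatment could be higher; that would weaken the rate test more than a within-unit interaction. The consequence is confined to the personalisation clause of hypothesis 3. The sample size and the primary QoL comparison are unaffected.

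**What to change.** Pre-specify one secondary, exploratory analysis before outcome data are examined: treatment received (surgery versus PET) modelled on arm, baseline fitness (age, Charlson, ADL/IADL), stage and arm × fitness, in the unit-clustered GEE framework already planned. Report it beside the rates as the evidence on the personalisation clause. Otherwise restrict hypothesis 3 to a change in overall rates.

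Three details matter.
- If a score from the Age Gap algorithm is also used, report that result as agreement with the tool, since the intervention arm was given that tool.
- Label any parallel chemotherapy analysis descriptive. Its population is defined by surgery and pathology that arise after randomisation, so it is not a clean randomised contrast.
- Adding ADL/IADL as a further QoL subgroup is optional.

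The cost is wording and one or two more exploratory tests. The data for the surgery/PET analysis are already collected in both arms.
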